### Study type

The study is a parallel, two-armed cluster randomised trial (PCRT) evaluating the efficacy of the In2Care® mosquito trap for reducing incidence of dengue infection over a 2-year period using 4 consecutive months of treatment each year.

Previous studies have estimated that, to account for the unpredictable spatio-temporal heterogeneity in dengue transmission, PCRTs are the most effective study design and that a larger number of clusters with fewer children per cluster provide the optimal strategy—in effect, a bet-hedging approach for a statistically sufficient coverage of an area [31]. In order to attempt to control for the spatial heterogeneity in dengue occurrence, 46 areas (hereafter referred to as “clusters”), each of approximately 200 m in radius, will be pre-selected. Twenty-three clusters will be assigned to the treatment arm with In2Care® traps and 23 to the control arm without traps. Cluster sites assigned to treatment versus control arms will be matched according to retrospective incidence of reported dengue clinical cases over the previous 5 years and human population density (See Stratification scheme below). Because of ‘edge effects’, where individuals near the periphery of the treatment area will be potentially subject to contact with mosquitoes coming from neighbouring non-treated areas, we will implement the “fried egg” design [32] whereby we will assess sero-conversion only in children resident at least 50 m from the treatment zone edge. Thus, whilst we will implement In2Care® traps throughout a 200 m radius circle, we will only consider sero-conversion in children within a 150 m radius (Fig. 1). One hundred schoolchildren (between 6 and 16 years of age) will be recruited for repeated sero-conversion observation within the inner circle of each of the 46 clusters (See Sample size calculations below). As the population density in clusters will vary, it is possible that there will not be sufficient children within a prescribed area. In this case, we will increase the circle radius to reach the required sample number.

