### Stratification scheme

Clusters will be stratified according to historical dengue incidence and population density. In the Philippines, a *barangay* is the smallest administrative division in the Philippines (urban or rural), but which can be subdivided into *puroks* (zones) consisting of 20 to 50 households depending on the location and density of the households in an area. The previous 5 years of dengue incidence data at the *purok* administrative unit level will be acquired from the Philippines Integrated Disease Surveillance and Response (PIDSR) system to identify relative defined ‘hotspots’ and ‘coldspots’ of dengue activity during that period. This information will be entered into the Disease Data Management System (DDMS+) (see Data management below) along with information on geography, population density, and infrastructure at the *barangay* level. This will generate maps with which to choose clusters for the intervention study and assign clusters to either treatment or control groups according to broad similarities.

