### Recruitment

In each *barangay* pre-selected to participate in the study, Research Institute for Tropical Medicine (RITM) team members will hold general information meetings on the project with the population in the presence of the community (*barangay*) health workers (BHWs) and local public health officials. Because the volunteers to be recruited are of school age, additional information meetings will be held in the local schools. Once clusters are identified and randomly assigned with appropriate stratification, the study team will perform household visits with the Lipa City public health staff and respective area BHWs. The visit will explain the study and study protocol in detail and request individual informed consent/assent for periodic saliva sampling and mosquito trap placement by each household head (In2Care® and/or GATs) in and around participant’s houses (See Ethics approval and consent to participate below).

Following signed consent, a short questionnaire pertaining to the participant will be completed and the individual assigned a unique identifier barcode. The questionnaire will be completed on paper including details on: name, address, age, sex, whether having received the Dengvaxia® vaccine (and if yes, how many injections) or not, and the attending school and year (grade). The individual’s barcode will be placed next to their name on the consent form and kept in a separate file. Subsequent samples will also be labelled with a unique barcode and linked back to the individual’s barcode in the questionnaire.

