### Statistical analyses

#### Classification of dengue incidence as ‘hot’, ‘intermediate’, and ‘cold’ spots

Dengue incidence for the previous 5 years will be acquired at the *purok* level, and the midpoint of the *purok* used as the geographical coordinate representing the *purok*. Population density at the *barangay* level will be acquired. Hot/coldspot classification of dengue incidence rate will be achieved through analysis using Kulldorff’s scan statistic in SaTScan™ (version 9.1.1) (http://www.satscan.org/) [40]. A discrete Poisson model will be used to analyse the spatial distribution of dengue cases using all 5 years of incidence data, with year as the analysis time unit and population density as a covariate. Within SaTScan™, an infinite number of cluster circles are generated with a minimum size diameter set to 300 m, the approximate size of the future clusters. A maximum value will initially be set to 1 km and then altered as a function of the number and type (hot/cold) of clusters detected. SaTScan™ identifies hot or cold spots that represent either more or less than the expected dengue cases compared with the entire study area. SaTScan™ then calculates the relative risk of observed hot and coldspots, and statistical significance of these spots is determined using a likelihood ratio test. Only spots with no geographical overlap will be accepted. Areas that are neither hotspots nor coldspots will be classified as intermediate. Hot and cold spots will contain a variable number of *purok*s and it is possible, and indeed likely, that hot and cold spots vary year to year. Therefore, *purok*s will be classified by annual similarity, in other words year 1 in hotspot, year 2 not, year 3 coldspot, and so on. In this way *purok*s can be classified into a risk designation and matched for treatment and control site selection.

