#### Sero-conversion

Sero-conversion of individuals to DENV will be analysed yearly using three saliva samples taken from each individual during each year (six total samples per volunteer). Because there are repeated measures from the same individual, sero-conversion is analysed using a generalised linear mixed model (GLMM) with ‘individual’ as a random factor. We will also include cluster ID, school, and occurrence (yes/no) of any public health mosquito control intervention performed in the cluster, and when, as random factors. Sero-conversion will be considered both as 1) a four-fold titre rise in DENV IgG optical density (OD) from baseline to post-treatment (year 1 or 2) samples, thus classifying individuals into yes/no (Y/N) sero-conversion, and 2) the actual change in OD without the restrictive definition of a four-fold increase. This double analysis will enable assessment of change in IgG OD beyond that using the classical threshold of an arbitrary four-fold increase. The Y/N IgG OD analysis will use logistic regression and the latter OD measure log-linear regression. Time (Post1 and Post2 for Y/N logistic regression; Pre-, Post1, and Post2 for log-linear regression), treatment (intervention Y/N), age (continuous), sex (male/female), vaccination status (0, 1, 2, 3 inoculation categories), and site (*purok*) risk (baseline seropositive prevalence rate) will be the explanatory variables. All analyses will be performed using Genstat version 15 [41].

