#### Adult mosquito spatial distributions (relative densities) using GATs

Weekly adult mosquito catches will be analysed by fitting a GLMM with the response variable as mosquitoes/trap/week, time (week), and intervention (Y/N) as fixed effects, and cluster ID and cluster risk designation as random effects. In addition, we will include occurrence of any public health mosquito control intervention performed in the cluster by counting the numbers of days during the 2 month inter-saliva sampling period when mosquito numbers could have been affected by such a control intervention (up to 14 days maximum post-control) as a random factor. We will test for over-dispersion in the response variable and, if it exists, an over-dispersion parameter will be estimated and applied. Otherwise, a Poisson distribution will be assumed. Two models will be constructed, one for each *Aedes* dengue vector species.

Additionally, a second series of analyses involving the distance of GATs from the nearest In2Care® trap will be analysed using log-linear regression, fitting the actual Euclidean distance in metres as a continuous variable. Because the extent to which an area is built up can impede mosquito flight (i.e. barriers), each cluster will be categorised into an urban typology (categorical building density) and this will be fitted as a factor in the analyses.

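### The sero-conversion model leaves out the factors on which clusters are allocated, at some cost in power, and one allocation sentence lacks a random element

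*Protocol article*

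**What the plan says.** **Allocation factors.** Study type says that sites in the two arms will be "matched according to retrospective incidence of reported dengue clinical cases over the previous 5 years and human population density". Stratification scheme says: "Clusters will be stratified according to historical dengue incidence and population density". The section on hot, intermediate and cold spots builds a classification from five years of incidence so that puroks can be "classified into a risk designation and matched for treatment and control site selection".

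**Sero-conversion model.** The fixed terms are time, treatment, age, sex, vaccination status and site risk, and the list closes with "risk (baseline seropositive prevalence rate) will be the explanatory variables". The random terms are individual, cluster ID, school and public health mosquito control. No term stands for stratum, pair, risk designation, historical incidence or population density.

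**GAT (adult mosquito) model.** This one enters "cluster ID and cluster risk designation as random effects". Population density is not among its terms.

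**Allocation rule.** Study type opens with "The study is a parallel, two-armed cluster randomised trial (PCRT". Recruitment says: "Once clusters are identified and randomly assigned with appropriate stratification". Stratification scheme says that maps will be used to choose clusters and to "assign clusters to either treatment or control groups according to broad similarities".

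**The concern.** When allocation is balanced on a factor that predicts the outcome, the two arms resemble each other more than under simple randomisation, so the treatment estimate varies less. An analysis that omits the factor still counts its variance as error. The standard error is then too large for the design, the true type I error falls below the nominal 5%, and power is lost. The Study limitations section names spatio-temporal heterogeneity in dengue as a major worry, so it matters whether the analysis uses the information that the design collects to deal with it.

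The allocation wording is a separate matter. The section that defines the scheme describes assignment by similarity and does not mention chance, while two other sections state randomisation. A reader cannot tell from that section how arms are assigned.

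**Working it through.** **1. The plan's own figure.** The Sample size section gives p0 = 0.03, p1 = 0.015, p = 0.0225, Zα = 1.96 and Z1–β = 1.2816.

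n = 2(1.96 + 1.2816)² × 0.0225 × 0.9775 / 0.015² = 2054.3

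The stated 2054 per arm reproduces and is not in dispute here.

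**2. Inputs for the check.** From the document: c = 23 clusters per arm, and m = 2054/23 = 89.3 evaluable children per cluster. Assumed, because the document gives neither: the between-cluster CV, k, and the share r of between-cluster variance that the allocation factors explain.

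**3. Formula calculation (Hayes–Bennett, with the c − 1 correction).**

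- V(k²) = p0(1 − p0)/m + p1(1 − p1)/m + k²(p0² + p1²) = 0.000491 + k² × 0.001125
- Power = Φ{ √[(c − 1)(p0 − p1)²/V] − 1.96 }

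For k = 0.5 and r = 0.6:

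- Unmatched design, no adjustment: V = 0.000773, √(22 × 0.000225/0.000773) = 2.53, power 71.6%.
- Matched design, strata modelled: k² falls to 0.25 × 0.4 = 0.10, V = 0.000604, the root is 2.86, power 81.7%.
- Matched design, strata ignored: the estimate has the smaller variance but is judged against the larger one. Power = Φ{ [0.015√22 − 1.96√0.000773] / √0.000604 } = Φ(0.646) = 74.1%.

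The right comparison for this trial is the last two lines, 74.1% against 81.7%, a loss of about 8 points. Taking 71.6% as the starting point would credit the analysis with a gain that the matching has already delivered.

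**4. Simulation.** 23 matched pairs, 89 children per cluster and 20,000 replicates, with a two-sample cluster-level t-test (matching ignored) against a paired one (matching used).

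| CV | Share explained | Type I, ignored | Type I, used | Power, ignored | Power, used |
|---|---|---|---|---|---|
| 0.25 | 60% | 4.2% | 5.2% | 86.2% | 86.2% |
| 0.5 | 0% | 5.2% | 5.3% | 74.4% | 72.2% |
| 0.5 | 30% | 3.7% | 4.8% | 75.2% | 76.1% |
| 0.5 | 60% | 2.8% | 4.9% | 76.0% | 80.4% |
| 0.5 | 90% | 1.6% | 4.8% | 77.4% | 84.9% |
| 0.75 | 0% | 4.8% | 4.8% | 58.8% | 56.8% |
| 0.75 | 60% | 1.8% | 4.6% | 60.3% | 70.6% |
| 0.75 | 90% | 0.6% | 4.5% | 62.1% | 81.0% |

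At CV 0.5 with 60% explained, the loss is 80.4 − 76.0 = 4.4 points. With the formula's 8 points, this gives the range of 4 to 8. At CV 0.75 with 60% explained, the simulated loss is about 10 points. At CV 0.25 it is nil. When matching explains nothing, the paired analysis loses about 2 points.

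**5. Credit for baseline sero-prevalence.** Neither calculation gives any. As an illustration, suppose that the covariate already captures half of what the strata would. At k = 0.5 the formula in step 3 then goes from 74.0% (k² = 0.2125) to 76.5% (k² = 0.175) when the strata explain 30%, and from 76.5% to 81.7% (k² = 0.10) when they explain 60%. The remaining gain is about 2.5 to 5 points.

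**6. Why not pair terms.** A pair would carry about 89.3 × (0.03 + 0.015) = 4.0 events. Twenty-three pairs would take 22 of the 46 − 2 = 44 cluster-level degrees of freedom.

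**The case against.** **The model already adjusts for site risk.** Baseline sero-prevalence reflects past infection in the sampled children and does not depend on case reporting, which the Setting section describes as substantially incomplete. It could be a good proxy for historical risk. This stands in part and shrinks the loss, as step 5 shows. It does not supply a density term. Density does enter the scan statistic as a covariate, but the designation that results is not in the sero-conversion model.

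**The effect is modest and in the safe direction.** This stands. A reader might infer bias or false-positive risk, but the simulation shows type I error at or below about 5% throughout, and a randomised comparison stays unbiased.

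**The trial might be read as not randomised.** The document does not support that. The abstract and Study type both call it cluster randomised, Recruitment states random assignment with stratification, and matching is compatible with randomising within matches. The sentence in Stratification scheme may well mean grouping by similarity before random assignment. It does not say so, and that is all the point claims.

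**The GAT model's random effect might be read as wrong because hot, intermediate and cold make only three classes.** This does not hold either. The classification section groups puroks by their year-by-year pattern, which may give many more levels, so a random effect is defensible.

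**Conclusion.** The point holds as a mismatch between design and analysis that costs precision. Allocation uses historical incidence and population density. The sero-conversion model contains neither, nor any stratum built from them, and substitutes a related variable for the first only.

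At CV 0.5 with 60% of between-cluster variance explained, the cost is about 4 to 8 points of power before credit for baseline sero-prevalence. It is larger at a higher CV, and negligible if between-cluster variation is small or the matching is weak. The CV, the share explained and the overlap with sero-prevalence are all assumptions. A gain of 10 points (72% to 82%) might be inferred at the same values, but that comparison starts from an unmatched design and overstates the benefit.

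The allocation sentence is a contradiction in wording. It has no calculable size and says nothing about how allocation was actually done.

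**What to change.** 1. In the sero-conversion model, add the allocation strata (a small number of risk-designation groups) and population density as cluster-level covariates, and keep baseline sero-prevalence.
2. In the GAT model, add population density. The risk designation is already there and may stay as a random effect.
3. Do not use 23 pair indicators, given the degrees of freedom and events per pair in step 6.
4. In Stratification scheme, state that clusters are grouped by similarity and then randomly assigned to arms within those groups, so that it agrees with Study type and Recruitment.

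The cost is a change of wording in the protocol and analysis plan and a few of the 44 cluster-level degrees of freedom. No new data are needed, since incidence and density are already to be acquired for site selection.

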#### Adult mosquito spatial distributions (relative densities) using GATs

Weekly adult mosquito catches will be analysed by fitting a GLMM with the response variable as mosquitoes/trap/week, time (week), and intervention (Y/N) as fixed effects, and cluster ID and cluster risk designation as random effects. In addition, we will include occurrence of any public health mosquito control intervention performed in the cluster by counting the numbers of days during the 2 month inter-saliva sampling period when mosquito numbers could have been affected by such a control intervention (up to 14 days maximum post-control) as a random factor. We will test for over-dispersion in the response variable and, if it exists, an over-dispersion parameter will be estimated and applied. Otherwise, a Poisson distribution will be assumed. Two models will be constructed, one for each *Aedes* dengue vector species.

Additionally, a second series of analyses involving the distance of GATs from the nearest In2Care® trap will be analysed using log-linear regression, fitting the actual Euclidean distance in metres as a continuous variable. Because the extent to which an area is built up can impede mosquito flight (i.e. barriers), each cluster will be categorised into an urban typology (categorical building density) and this will be fitted as a factor in the analyses.

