### Outcomes

The principle evaluation criterion is the epidemiological efficacy read out: dengue infection sero-conversion. Sero-conversion to dengue virus exposure will be measured by an enzyme-linked immunosorbent assay (ELISA) for immunoglobulin (Ig)G titres using repeated saliva samples taken sequentially during three cross-sectional studies at months 0, 3 (end of month 2), and 5 (end of month 4) during the intervention (In2Care® trap placement) period each year in both treatment and control sites. These time points are designated Pre-, Post1, and Post2 within each year.

The secondary evaluation criterion is the entomological read out. To measure the impact of the In2Care® traps on the adult mosquito population densities, 20 GATs will be placed in each of 10 randomly selected treatment and 10 control sites matched with intervention sites for historical dengue incidence. *Aedes* spp. (both *Ae. aegypti* and *Ae. albopictus*) adults will be counted and identified in the GATs once each week beginning 2 weeks before intervention, throughout the intervention period, and 2 weeks post-intervention. Traps will be placed both inside and outside 10 randomly selected houses within each site. Traps placed outside will be positioned against the wall of the house in an area with shelter from direct sunlight. Traps placed inside the house will be positioned in a suitably unobstructed area but where there is air movement.

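### The GAT-to-In2Care distance analysis lists no GAT or house effect, so fitting weekly counts with the listed terms would understate the standard error of the distance slope (minor)

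*Protocol article*

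**What the plan says.** The section of the protocol article on adult mosquito spatial distributions describes two GAT analyses.

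- **Main catch model.** Weekly catches go into a GLMM with week and intervention as fixed effects and "cluster ID and cluster risk designation as random effects". A term for routine mosquito control activity is also random. If the counts are over-dispersed, "an over-dispersion parameter will be estimated and applied".
- **Distance analysis.** This is introduced separately, as an addition to the main model. As to method, the article says that it "will be analysed using log-linear regression, fitting the actual Euclidean distance in metres as a continuous variable". The only other term named is at cluster level: "each cluster will be categorised into an urban typology (categorical building density) and this will be fitted as a factor in the analyses".

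Neither description lists a term for the individual GAT or for the house. The article does not give the response or the unit of analysis (weekly count, or total per GAT) for the distance analysis.

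Under Outcomes, 20 GATs go into each of 10 treatment and 10 control sites, at ten houses per site, both indoors and outdoors. Catches are counted "once each week beginning 2 weeks before intervention", and counting goes on until a fortnight after the traps are taken away. The same section makes the entomological read-out the secondary criterion.

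**The concern.** Distance from a GAT to the nearest In2Care trap differs between GATs but hardly changes from week to week. The information on the slope therefore comes from the number of GATs and houses. Counting the same GAT again adds little if some locations catch persistently more mosquitoes than others. A model on weekly counts without a GAT or house term treats every trap-week as new evidence on distance.

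Three listed terms might seem to deal with this, but do not:

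- The typology factor is constant within a cluster, so it cannot absorb differences between traps in that cluster.
- A cluster random effect has the same limit. It suits the main intervention comparison, where treatment is assigned by cluster, but the distance slope is estimated largely within clusters.
- An over-dispersion parameter rescales the variance of single weekly counts. It does not represent correlation between counts from the same GAT.

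At stake is a spurious or over-precise gradient of catch against distance. Such a gradient could be read as evidence on the reach of the traps, and the Discussion treats trap density as a practical obstacle.

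**Working it through.** The article states no sample size, standard error or error rate for this analysis, so there is no figure to reproduce. The check is of the consequence of the listed terms.

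**Inputs from the article (Outcomes; Intervention)**
- Treated sites with GATs: 10, with 20 GATs each, so 10 × 20 = 200 GATs. They stand at 10 × 10 = 100 houses, two per house.
- Counts per GAT per season: four months is about 17 weeks, plus 2 + 2 weeks, so about 21.
- Trap-weeks per season in treated sites: 200 × 21 = 4,200.

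**Assumed, because the article gives no figure:** the correlation ρ between weekly counts of one GAT, and the log-scale SDs between clusters, houses and GATs.

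**Step 1: design effect.** With a covariate constant within GAT and m counts per GAT, DE = 1 + (m − 1)ρ. The standard error is understated by √DE, and the true two-sided error of a nominal 5% test is 2[1 − Φ(1.96/√DE)]. With m = 21:

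| ρ | DE | √DE | True error |
|---|---|---|---|
| 0 | 1.0 | 1.00 | 5% |
| 0.01 | 1.2 | 1.10 | 7% |
| 0.05 | 2.0 | 1.41 | 17% |
| 0.10 | 3.0 | 1.73 | 26% |
| 0.30 | 7.0 | 2.65 | 46% |

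For example, at ρ = 0.10: DE = 1 + 20 × 0.10 = 3.0, and 1.96/1.73 = 1.13, giving 26%.

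**Step 2: does a cluster effect cure it?** Data were simulated with no true distance effect, 21 weekly counts per GAT and assumed trap SDs of 0.1 to 0.5. Rejection rates at a nominal 5% were:
- weekly counts, no cluster effect: about 40–53%
- weekly counts, cluster effects but no GAT term: about 14–47%
- totals per GAT with cluster effects: about 5–15%
- no trap or cluster variance: about 5%

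**Step 3: sensitivity to the assumptions.** A second set-up had 10 clusters × 10 houses × 2 GATs × 21 weeks. The mean was 1 mosquito per GAT-week with gamma week-to-week variation (shape 1). Distance was uniform on 2–25 m and shared by the two GATs of a house. The models were Poisson with Pearson scale, with 300 data sets per row.

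| SD cluster/house/GAT | Weekly, typology only | Weekly, cluster effects | GAT totals, cluster effects |
|---|---|---|---|
| 0/0/0 | 8% | 9% | 8% |
| 0.3/0.1/0.1 | 27% | 12% | 8% |
| 0.3/0.3/0.3 | 33% | 28% | 8% |
| 0.5/0.5/0.5 | 52% | 53% | 16% |

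The columns share data sets, and the Monte Carlo standard error at 5% is √(0.05 × 0.95/300) = 1.3 points. Repeating the first row with 1,000 data sets gave 5%, so its 8–9% is simulation noise.

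A third set-up used 17 counts, no house effect and cluster/GAT SDs from 0.3/0.1 to 0.5/0.7. It gave 19–52% without and 6–51% with cluster effects, and 5–10% for GAT totals.

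**Reading.** Cluster effects help when trap-level variation is small and hardly at all when it is large. Totals per GAT remove most of the inflation. The 16% in the last row arises because two GATs share a house and a distance, which is why a house term is also needed.

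**The case against.** The strongest objection is that the article is merely brief here. A reader might infer that it prescribes a plain regression treating weekly counts as independent. It does not say that. The unit of analysis is not stated, and nothing says that the random terms of the preceding model are dropped. In the Sero-conversion section the same term is used inside a mixed model: "sero-conversion is analysed using a generalised linear mixed model (GLMM) with ‘individual’ as a random factor", followed by "The Y/N IgG OD analysis will use logistic regression and the latter OD measure log-linear regression". The label therefore does not by itself exclude random effects. The article also condenses a fuller protocol, and an unseen analysis plan may settle the matter.

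Much of this stands. Cluster effects may well be intended, and if catches are totalled per GAT, the repeated weeks are no longer an issue. The objection does not reach the remaining gap, however. The article does name a method and its terms, and carrying over the main model's random effects would still leave no GAT or house term.

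Two further inferences lack support. One is that the standard errors are certain to be far too small, so that a false gradient would be declared. The article gives no variance or correlation, and with very small trap-level variation the cluster-effects reading is nearly harmless (6% in the mildest simulated case). The other is that control-site GATs would be entered, so that distance would stand in for trial arm. Nothing in the article says so.

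**Conclusion.** The point holds conditionally. If weekly counts are fitted with the terms the article lists, the standard error of the distance slope is too small whenever catches vary persistently between traps or houses, whether or not cluster effects carry over. Under assumed trap SDs of 0.1 to 0.5 and 21 counts, type I error is roughly 14–47% with cluster effects only and 40–53% without. Other plausible assumptions move the lower ends down to about 6% and 19%. With no trap or cluster variance the error stays at 5%. The direction follows from the design, but the size rests on variances the article does not supply.

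Severity is minor. This is an additional analysis of the secondary outcome, with no stated test or decision attached. It does not touch the sero-conversion result or the main intervention comparison of catches.

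**What to change.** State the unit of analysis and fit distance in a GLMM of the same family as the main catch model, with random effects for cluster, house within cluster, and GAT within house. An acceptable alternative is to analyse totals per GAT with cluster and house effects. Restrict the analysis to GATs in treated clusters during the weeks when In2Care traps are deployed (about 17 of the 21 counts), since distance has no clear meaning while no trap is standing.

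This takes a sentence or two in the analysis section and no new data, provided each catch record carries GAT and house identifiers. The price is a wider interval for the distance slope.

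### The GAT-to-In2Care distance analysis names no random term, and those it might inherit stop at cluster level, so repeat counts from one trap and house would count as independent evidence on distance

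*Protocol article*

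**What the plan says.** The section on adult mosquito spatial distributions describes two analyses of the GAT catches.

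- **First analysis.** A GLMM of mosquitoes per trap per week, with week and intervention fixed, "and cluster ID and cluster risk designation as random effects". Days affected by public control activity in the cluster enter as a further random factor. Over-dispersion will be tested for and, "if it exists, an over-dispersion parameter will be estimated and applied".
- **Second analysis.** It opens "Additionally, a second series of analyses involving the distance of GATs from the nearest In2Care® trap" and "will be analysed using log-linear regression, fitting the actual Euclidean distance in metres as a continuous variable". To allow for buildings that impede flight, "each cluster will be categorised into an urban typology (categorical building density) and this will be fitted as a factor in the analyses". Distance and typology are the only terms listed. The unit of analysis is not stated.

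The Outcomes section gives the layout: 20 GATs in each of 10 treatment and 10 control sites, placed inside and outside 10 "randomly selected houses within each site", and counted weekly from two weeks before the intervention to two weeks after it.

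**The concern.** The two explanatory variables vary at different levels of a nested design, and neither level is the weekly count. Provided a GAT stays where it is put during a season, its distance to the nearest In2Care trap is the same every week, and the inside and outside GATs of one house have similar distances. Typology takes one value per cluster. In the treated sites, thousands of weekly counts therefore rest on about 100 houses and 10 clusters.

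A model without terms for house and GAT takes each weekly catch as new evidence on distance. Some houses attract more mosquitoes than others for reasons unrelated to In2Care traps, and such a model can report those stable differences as a distance effect. An over-dispersion parameter scales the variance of single counts. It does not represent the correlation between counts from the same trap or house.

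At stake is the only analysis described of how the catch changes with distance from an In2Care trap. The Discussion treats workable trap density as an open problem, so a spurious slope, or a slope with too narrow an interval, could mislead readers on it.

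**Working it through.** **Plan's own figure.** The article gives no sample size, ICC, variance component or standard error for GAT counts. Its one sample-size figure, 2054 children per arm, reproduces: 2 × (1.96 + 1.2816)² × 0.0225 × 0.9775 / 0.015² = 2054.3. It has no bearing here.

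**Structure (Outcomes; Intervention).**
- Each site has 10 houses × 2 = 20 GATs, so 10 treated sites have 200 GATs in 100 houses.
- Four months is about 16–17 weeks. Adding 2 weeks on each side gives 20–21 counts per GAT per year.
- At 21 weeks this is 20 × 21 = 420 counts per cluster and 200 × 21 = 4,200 in the treated sites per year.

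**Closed form.** For a covariate that is constant within a group of m counts, the standard error that ignores the grouping is too small by √(1 + (m − 1) × ICC). The ICCs are assumptions.

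| Covariate | m | Factor at each assumed ICC |
|---|---|---|
| Distance, repeats within GAT | 21 | 0.05: 1.41; 0.10: 1.73; 0.20: 2.24; 0.50: 3.32 |
| Distance, if both GATs of a house share it | 42 | 0.05: 1.75; 0.10: 2.26; 0.20: 3.03; 0.50: 4.64 |
| Typology, no cluster term | 420 | 0.005: 1.76; 0.01: 2.28; 0.05: 4.69; 0.10: 6.55 |

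On repeats within GAT alone, the ceiling is √21 = 4.58, and a factor of 2 needs an ICC of 3/20 = 0.15. If only the roughly 17 weeks with In2Care traps in place are used, the distance factors at ICC 0.05 and 0.50 become √1.8 = 1.34 and √9 = 3.00.

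**Simulation.** It used 10 clusters × 10 houses × 2 GATs × 21 weeks with no true effect. Distance was drawn separately for each GAT, uniformly from 1 to 25 m; typology had two categories of five clusters each. The model was Poisson with an estimated over-dispersion parameter, fitted to 150 datasets per setting. Cluster, house and trap SDs were set equal. Entries are the true standard error divided by the mean reported one. The cluster term was fitted as fixed effects, standing in for the random term.

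| SD of each level; mean catch | Distance, no cluster term | Distance, cluster term fitted | Typology, no cluster term |
|---|---|---|---|
| 0.1; 1.5 | 1.33 | 1.21 | 3.19 |
| 0.2; 1.5 | 2.01 | 1.87 | 4.80 |
| 0.3; 1.5 | 2.65 | 2.40 | 6.77 |
| 0.5; 1.5 | 4.01 | 4.27 | 9.58 |
| 0.3; 0.3 | 1.64 | 1.55 | 3.97 |

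The third column carries the argument: fitting cluster leaves the distance problem almost unchanged, because the omitted correlation lies at house and GAT level.

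**Effect on the test.** A separate simulation with cluster fitted, one season of 17 weeks and a mean catch of 1 gave type I error of 23%, 30%, 37% and 59% against a nominal 5%. The house/trap/cluster SDs were 0.2/0.1/0, 0.3/0.2/0, 0.3/0.2/0.3 and 0.5/0.3/0.5. The true standard error was 1.6 to 3.6 times the reported one.

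**The case against.** A reader might infer that the authors chose a plain regression with every random effect dropped. The text does not support that. It lists no random term for the distance series, but it does not say that the earlier ones are removed. The article's own usage points the other way. In the Sero-conversion section, "The Y/N IgG OD analysis will use logistic regression and the latter OD measure log-linear regression", yet the same paragraph says "sero-conversion is analysed using a generalised linear mixed model (GLMM) with ‘individual’ as a random factor". There the term names the form of the response, not the absence of random effects. A condensed article may also leave the random terms of an additional analysis to the full plan.

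This argument stands, but it rescues only part of the analysis. If the first model's terms carry over, they are cluster ID, cluster risk designation and control activity in the cluster. None separates one house or GAT from another. Carrying them over should deal with typology, but not with distance. The Sero-conversion paragraph itself justifies a random factor for the individual by the repeated measures, and repeated counts from a GAT have the same structure.

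Three further objections limit the size.

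- **Unit of analysis.** One value per GAT per season fits the text and would remove the weekly repeats. Pairing within house would remain, with a factor of at most √2 = 1.41 for distance. Weekly rows are the likelier reading, since catches are weekly and the first model's response is per week, but this is not stated.
- **Placement.** Traps are removed and stored after each season, and nothing says that they return to the same positions. The figures above therefore cover one season.
- **Inside and outside GATs.** At one In2Care trap per 1000 m², a square grid has spacing √1000 = 31.6 m and a mean distance to the nearest trap of about 0.383 × 31.6 = 12 m. A few metres between two GATs is not negligible on that scale, so treating their distances as equal is an approximation. The simulation tabled above does not rely on it.

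**Conclusion.** The point holds as a gap in the specification. The listed terms omit the levels at which distance varies, and inheriting the first model's random terms would not supply them.

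With weekly rows and an over-dispersion parameter, the distance standard error in one season would be too small by roughly 1.3 to 4 times. The two distance columns of the simulation run from 1.2 to 4.3. This rests on assumed SDs of 0.1 to 0.5 on the log scale, assumed mean catches, and an analysis confined to treated sites. It is a range under assumptions, not a property of the plan.

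The understatement for typology is conditional: it arises only if no cluster term is fitted, and could then be larger (3.2 to 9.6 in the simulation at a mean catch of 1.5).

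A reader might go on to infer a fixed, known error in both effects, or doubt about the trial's main result. Neither follows. This analysis is additional to the secondary, entomological criterion. The sero-conversion comparison and the between-arm comparison of mosquito density do not depend on it, and the article attaches no test or decision threshold to the distance slope. It should be corrected, but it does not threaten the trial.

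**What to change.** Replace the description of the distance series with one that states the following:

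- it is a GLMM of weekly catch per GAT;
- it has random intercepts for cluster, house and GAT, the last two being additional to the terms of the first GAT model;
- week is a fixed factor;
- distance is continuous;
- typology is tested against between-cluster variation;
- the distance slope is reported with the interval from this model.

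This takes about one sentence and needs no new data, provided house and GAT identifiers are kept with each count. The cost is wider intervals. Typology will be imprecise with about 10 treated clusters behind it, and the report should say so.
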